#### Primary Aim

The primary aim is to examine differences in psychological (craving, sense of presence, and social presence) and physiological (eye gaze, HR, and EDA) responses between young adults who currently vape and those who have never vaped during exposure to VR vaping cues presented with and without social pressure. We hypothesize that vapers will exhibit stronger craving, a greater sense of presence and social presence, increased visual attention to vaping cues, and heightened physiological arousal compared with nonvapers across both VR scenes. We further expect that both groups will show stronger psychological and physiological responses in the social pressure condition than in the no pressure condition.

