## Methods

### Study Design

This study will examine individuals’ psychological, behavioral, and physiological responses to e-cigarette cues in VR among young adults aged 18 to 21 years. We focus on this age range because the transition into early adulthood often brings increased exposure to vaping-related social contexts (eg, college gatherings) [27], and this pilot allows us to first test the paradigm in adults before adapting it for adolescent populations. A between-subjects design is used to compare current e-cigarette users and nonusers, with a within-subject, counterbalanced component to assess 2 cue conditions (with and without social pressure). This mixed-design approach enables testing of cue effects and group differences while controlling for individual variability.

Prior VR nicotine cue reactivity studies have reported medium-to-large effects for the response difference between user and nonuser groups [17,28]. Based on the relevant research and using G*Power 3.1 (Heinrich Heine University Düsseldorf) for a 2 (group: vapers vs nonvapers)×2 (cue condition: social pressure vs no social pressure) mixed design, we powered the study for the group × cue condition interaction (group×cue condition) assuming a medium effect (*f*=0.25; partial η-squared ≈ 0.06; power=0.80). We assumed a within-participant correlation of *r*=0.50 between cue conditions and a nonsphericity correction of *ε*=1.0 (sphericity is not applicable with 2 within-subject levels). This yields a minimum required sample of 34 (n=17 per group). To ensure robustness and account for potential data loss (eg, eye-tracking dropout and physiological artifacts), we plan to recruit 40 participants in total (n=20 vapers and n=20 nonvapers).

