### Study Population and Study Flow

This study will recruit young adults aged 18 to 21 years living in or around New Haven, Connecticut. Recruitment efforts will focus on two distinct groups: (1) individuals who currently use nicotine-containing e-cigarettes, defined as use on 10 days or more within the past 30 days (*vapers*), and (2) individuals who report never having used nicotine-containing vapes (*nonvapers*). Participants who use nicotine in non–e-cigarette forms (eg, cigarettes and nicotine pouches) will not be excluded but will be assessed at baseline so that such exposure can be accounted for analytically. This design allows the comparison of psychophysiological cue reactivity between vapers and nonvapers, as well as the exploration of predictors of future initiation risk among nonvapers.

Eligibility will require participants to be fluent in English and able to provide informed consent. Exclusion criteria include self-reported photosensitive epilepsy, significant visual, hearing, or mobility impairment, current or recent (past 30 days) use of cannabis-containing e-cigarettes, current use of other illicit substances (eg, 3,4-methylenedioxymethamphetamine or ecstasy, and methamphetamine), nonmedical misuse of prescription drugs, or reliance on eyeglasses that are incompatible with VR eye-tracking hardware. These exclusions help reduce noise in psychophysiological responses that may arise from nonnicotine substances, ensuring clearer differentiation between the study groups. A total sample of 40 participants will be enrolled, which is sufficient for detecting medium group effects in VR cue-reactivity studies while accounting for potential data loss.

The study flow is shown in Figure 1. Eligible participants will complete a single laboratory session lasting approximately 1 hour. After providing informed consent and completing baseline questionnaires, participants will be fitted with a VR headset and biometric sensors. They will complete 3 VR scenes: a neutral baseline, a vaping cue scene without social pressure, and a vaping cue scene with social pressure in a counterbalanced order. Physiological data will be recorded continuously, and brief self-report measures (craving, presence, and social presence) will follow each cue scene. Participants will rate the system’s usability after finishing all the VR sessions. The session will conclude with a short semistructured interview, debriefing, and compensation.

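### The statement that 40 participants suffice for medium group effects is not supported: the power calculation covers only the interaction, and power for a medium vaper-versus-nonvaper effect is about 43%

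*Protocol article*

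**What the plan says.** Under Study Design, the protocol article names the effect it was sized for: "we powered the study for the group × cue condition interaction". The inputs follow: "assuming a medium effect (*f*=0.25; partial η-squared ≈ 0.06; power=0.80"), and "We assumed a within-participant correlation of *r*=0.50 between cue conditions". The result is a minimum of 34 (17 per group), raised to 40 (20 per group) to allow for data loss. The effect size is motivated by earlier VR studies that "reported medium-to-large effects for the response difference between user and nonuser groups".

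Under Study Population and Study Flow, the result is restated for a different effect: "A total sample of 40 participants will be enrolled, which is sufficient for detecting medium group effects in VR cue-reactivity studies". The sentence adds that possible data loss is covered. No calculation for a group effect is given.

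Under Primary Aim there are two hypotheses. The first is about group: "We hypothesize that vapers will exhibit stronger craving, a greater sense of presence and social presence", with more visual attention and arousal as well, in both scenes. The second is that both groups respond more strongly under social pressure. Neither is an interaction.

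**The concern.** In a 2×2 mixed design, the interaction and the group main effect have different error terms. The interaction is tested on within-participant differences between scenes, and the group effect on each participant's average over the scenes. A positive correlation between scenes makes the difference more precise and the average less precise. A sample size worked out for the interaction therefore says nothing direct about the group effect, even at the same f.

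The group contrast carries the study's stated objective, which is whether VR responses separate vapers from nonvapers. A reader of the sufficiency sentence would believe that a medium difference is likely to be detected. If power is well below one half, a true medium difference is more likely to be missed than found.

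**Working it through.** **Inputs from Study Design.** f = 0.25, r = 0.50, ε = 1.0, target power 0.80, k = 2 groups, m = 2 scenes, minimum N = 34, planned N = 40 (1:1).

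**Assumed input.** Alpha is not stated. I use 0.05 with the usual F test (two-sided), which step 1 supports.

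**Method.** Noncentral F with 1 and N − 2 degrees of freedom, in G*Power's default repeated-measures form.

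**Step 1: reproduce the protocol's figure (interaction).** λ = f²·N·m·ε/(1 − r). The multiplier m/(1 − r) is 2/0.5 = 4.
- N = 32: λ = 0.0625 × 32 × 4 = 8.0, power 78.1%
- N = 34: λ = 0.0625 × 34 × 4 = 8.5, power 80.7%
- N = 40: λ = 0.0625 × 40 × 4 = 10.0, power 86.9%

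The smallest even N reaching 80% is 34, as stated. The interaction calculation therefore reproduces, and alpha 0.05 is consistent with it.

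**Step 2: same inputs, group main effect.** λ = f²·N·m/(1 + (m − 1)r). The multiplier is 2/1.5 = 1.33, one third of that in step 1.
- N = 40: λ = 0.0625 × 40 × 2/1.5 = 3.33, power 42.9%
- N = 34: λ = 0.0625 × 34 × 2/1.5 = 2.83, power 37.2%
- N = 96: power 79.9%; N = 98: λ = 8.17, power 80.8%

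**Step 3: cross-check as a two-sample comparison.** f = 0.25 corresponds to d = 2f = 0.5 in a single scene. The average of two scenes has SD √((1 + 0.5)/2) = √0.75 = 0.866 in single-scene units. A normal approximation with 20 per group gives 44.7% power, and 48 per group for 80%, in line with step 2.

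**Step 4: sensitivity at N = 40, f = 0.25.**

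| Variant | Power |
|---|---|
| r = 0 | 58.7% |
| r = 0.3 | 48.1% |
| r = 0.5 | 42.9% |
| r = 0.7 | 38.7% |
| r = 0.5, one-sided 0.05 | 55.9% |

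None reaches 80%.

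**Step 5: what the sample can detect (r = 0.50).** The smallest f with 80% power is 0.394 at N = 40 (single-scene d = 2 × 0.394 = 0.79) and 0.429 at N = 34 (d = 0.86). At f = 0.40, power is 81.2% at N = 40 and 74.3% at N = 34.

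**The case against.** Several things can be said for the protocol.

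*The powered effect is disclosed.* Study Design says plainly that the interaction was powered, and its figure reproduces. The primary ANOVA includes that term, and the nonparametric fallback was chosen so that it can still be tested. This stands: powering the interaction is not in itself an error, and the fault lies in the later sentence.

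*Group effects may be loose wording for the interaction.* If so, the sentence still describes the wrong effect. The literature cited for the effect size and the first primary hypothesis both concern vapers against nonvapers.

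*Earlier effects were medium to large.* At f = 0.40 the full 40 are enough, though 34 are not. That stands for the upper end of the cited range, but the sentence says medium and says data loss is covered.

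*It is a pilot with a feasibility goal.* A pilot may be small. Here, though, the text makes an explicit claim of sufficiency on the back of a formal power calculation.

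Some stronger readings are tempting but not supported. A reader might infer that the whole primary aim is underpowered. The group difference is one of two primary hypotheses, and the other is a within-participant contrast to which this shortfall does not apply. A reader might take 34 as the expected number analysed. It is the minimum required sample, and no loss rate is stated. Nor does any text say that a non-significant group result would be read as no difference.

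**Conclusion.** The sufficiency statement is wrong as written if group effects has its plain meaning. For a medium group main effect, power is about 43% with all 40 analysed and 37% with 34, about half the 80% attached to the interaction. The sample reaches 80% only for a large effect, f of about 0.39 (0.43 at 34).

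The figures rest on the protocol's own f and r, on G*Power's default definition of f, and on an alpha of 0.05 that is assumed. The conclusion does not depend on r between 0 and 0.7, or on a two-sided rather than one-sided test.

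A reader might go further and conclude that the study must be re-powered on the group effect or enlarged to 98. The documents do not require that. The study is registered and enrolling, its interaction calculation is sound on its stated inputs, and the error is confined to one claim.

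**What to change.** Replace the sentence under Study Population and Study Flow with text along these lines, once the sponsor has confirmed the alpha used:

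> Forty participants will be enrolled. With f = 0.25, r = 0.50 and two-sided alpha 0.05, a minimum of 34 gives 80% power for the group-by-cue interaction; 40 allows for data loss. For the group main effect, 40 participants give about 43% power at f = 0.25 (37% if 34 are analysed), and 80% power only for f of about 0.39 or more (0.43 if 34 are analysed).

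The interaction calculation under Study Design can stay. The cost is wording and a less favourable stated figure; sample size, endpoints and analysis do not change. With 7 participants enrolled as of March 2026, the correction is best made before results are known.

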##### Primary Analyses

For the primary aim of examining differences in psychological and physiological responses between vapers and nonvapers during VR cue exposure with and without social pressure, a mixed-model ANOVA will be conducted. Group (vapers vs nonvapers) will serve as the between-subjects factor, and cue condition (social pressure vs no social pressure) as the within-subjects factor. If the assumptions of normality or homogeneity of variance are violated, nonparametric alternatives such as the aligned rank transform ANOVA [55] will be used to preserve the ability to test interaction effects within the mixed design. Follow-up pairwise comparisons will be conducted with Bonferroni-adjusted *P* values.

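### The primary ANOVA leaves out the counterbalanced scene order, so any first-to-second-scene shift stays in the error term of the cue-condition and interaction tests

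*Protocol article*

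**What the plan says.** Under Study Population and Study Flow, the single session of about an hour has a neutral baseline, "a vaping cue scene without social pressure, and a vaping cue scene with social pressure in a counterbalanced order". Study Design also calls the within-subject part counterbalanced.

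For the primary aim, "a mixed-model ANOVA will be conducted". Its factors are named: "Group (vapers vs nonvapers) will serve as the between-subjects factor, and cue condition (social pressure vs no social pressure) as the within-subjects factor". No order, period or sequence term appears there or in the aligned rank transform fallback. Order is also not among the examples of covariates listed under Secondary Analyses (age, gender, other substance use).

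The sample size uses the same two-factor layout. In Study Design, "we powered the study for the group × cue condition interaction", with f=0.25 and power 0.80. "We assumed a within-participant correlation of *r*=0.50 between cue conditions". The result is 34 participants (17 per group), and 40 are to be recruited to allow for data loss.

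**The concern.** With two cue scenes per person, this is a two-period, two-sequence design. Craving, skin conductance, heart rate and gaze could all drift between a first and a second exposure within the hour, through habituation, fatigue or growing familiarity with the headset. Counterbalancing keeps such a drift out of the mean scene contrast as long as the orders are balanced. It does not keep the drift out of the residual variance; only a term in the model does that.

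The tests at stake are the cue-condition effect and the group × condition interaction. Both are judged against the variability of each participant's scene difference. The omission could cost power, and it could distort the interaction estimate if vapers and nonvapers end up with different order splits.

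Because the article names the factors of the model, this is a stated model without a known design factor. It is not a detail merely left for a later plan.

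**Working it through.** **Inputs.** From Study Design: f=0.25, r=0.50, two groups, two conditions, N=34 required and N=40 recruited. Assumed: two-sided alpha 0.05 (not stated in the article) and the size of the order shift, p, in single-scene SD units (no figure in the article).

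**Reproducing the plan's figure.** For the within-between interaction, the noncentrality is λ = f²·N·m/(1−r) = 0.0625·N·2/0.5 = 0.25N, with 1 and N−2 degrees of freedom. Power is 0.781 at N=32, 0.807 at N=34 and 0.869 at N=40. The stated minimum of 34 reproduces, with little slack.

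**Same test on the difference score.** Let D = pressure scene − no-pressure scene. Var(D) = 2(1−r)·SD² = 1 SD² at r=0.50. The interaction is the group difference in mean D. Since λ = (N/4)·δ²/Var(D) = 0.25N, the powered effect is δ = 1.0 SD.

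**Effect of omitting order.** A shift p from first to second scene adds +p to D when the pressure scene comes second and −p when it comes first. With half the participants in each order and no order term, the error variance becomes 1+p², and λ becomes 0.25N/(1+p²).

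| Assumed shift p (SD) | 1+p² | Power, N=34 | Power, N=40 |
|---|---|---|---|
| 0 | 1.00 | 0.807 | 0.869 |
| 0.2 | 1.04 | 0.792 | 0.856 |
| 0.3 | 1.09 | 0.773 | 0.839 |
| 0.5 | 1.25 | 0.715 | 0.787 |

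This formula treats order as extra random noise. Under exact balance (10/10 in each group, N=40), the estimate is steadier than its inflated error term implies, so the true loss is a little smaller: simulated power is about 0.847 at 0.3 SD and 0.809 at 0.5 SD. For the same reason the test is conservative, with simulated type I error about 0.04 at 0.3 SD and 0.03 at 0.5 SD.

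**Bias when order splits differ by group.** If a fraction q of a group sees the pressure scene second, that group's mean D moves by p(2q−1). With q=0.6 in one group and 0.4 in the other (12/8 against 8/12), the interaction moves by p(0.2+0.2) = 0.4p, which is 0.2 SD at p=0.5, or a fifth of the powered 1.0 SD. Simulated type I error there is about 0.06. If both groups share the same split, the interaction is unbiased and only the cue-condition effect moves. With 10/7 in both groups it moves by p·3/17, about 0.09 SD at p=0.5.

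**Group main effect.** Each participant's average over the two scenes contains p/2 whatever the order. This cancels between groups, so a pure shift neither biases this comparison nor adds variance to it.

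**With order in the model.** Power is 0.805 to 0.806 at N=34 and 0.868 at N=40 with balanced orders, whatever the value of p. In the simulated unbalanced splits the bias disappears.

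**The case against.** Several parts of the case against carry weight.

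- **The shift sizes are assumptions.** At 0.2 to 0.3 SD the loss is 1 to 3 points, and at N=40 power stays above 0.80 up to about 0.4 SD. This stands.
- **The power loss depends on how r is read.** The article ties r=0.50 to the cue conditions and does not say whether order effects have been removed. If the planning SD and r are ordinary values from counterbalanced data, order variance is already inside Var(D), and adding p² counts it twice. The omission then forgoes a gain over the plan and does not cause a loss against it. This stands as a condition on the table.
- **A reader might infer that the omission produces false interactions.** The figures do not support that. Type I error is below 0.05 with balanced orders and only about 0.06 in the 12/8 against 8/12 case. The bias also requires splits that differ between groups.
- **A reader might infer that the 15% missing-data exclusion will unbalance the orders.** Nothing in the article links signal loss to order. The rule removes whole participants and concerns physiological data.
- **A reader might infer that order is not balanced within groups.** The article is silent on this, and the allocation list may sit in the full protocol, so the silence is not a defect.

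None of these points explains why a counterbalanced factor should be absent from a model whose factors are listed.

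**Conclusion.** The point holds as an inexpensive improvement to the stated primary model. An order shift, if there is one, stays in the error term of the cue-condition and interaction tests. On the reading that the planning values are free of order effects, the cost to interaction power is 1 to 3 points for shifts up to 0.3 SD and 8 to 9 points at 0.5 SD, slightly less under exact balance. Bias in the interaction is a chance outcome that depends on different order splits in the two groups. The comparison of vapers with nonvapers across both scenes is not affected by a pure shift.

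It would be too strong to say that the analysis is invalid or that an order term would settle all sequence problems. Carry-over that differs between the two scenes, such as craving raised by the party scene persisting into the store scene, biases the condition contrast even with balanced orders. If it also differs by group, it biases the interaction. An order term does not remove either.

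**What to change.** - Add scene order to every primary ANOVA: period (first or second cue scene) as a within-subject term and sequence as a between-subjects term. Carry the same terms into the aligned rank transform fallback. The cost is 1 to 2 degrees of freedom and about 0.001 to 0.002 in power.
- Report order counts by group among the participants analysed for each outcome.
- Report the vaper-nonvaper comparison from the first cue scene alone as a sensitivity check for carry-over. It uses half the data per person and compares each scene between smaller subgroups, so it is a check and not a replacement for the primary test.

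No new data are needed. With 7 participants enrolled by March 2026, the terms can still be fixed before analysis, which avoids a later choice over whether to adjust.

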**Figure 1. F1:**
[figure not shown]
Study flow graph. VR: virtual reality.

### Stimuli Design and Development

#### User-Centered Stimuli Design

##### Overview

We adopted a user-centered design (UCD) approach to ensure that the VR cue stimuli were both realistic and engaging for young adults [29]. Two focus groups (n=7; 6 females and 1 male; aged 18‐21 y) were conducted. Focus group participants were asked to indicate, on a scale of 1 (“least frequent”) to 5 (“most frequent”), the frequency with which they were in environments where vaping was present (mean 1.9, SD 1.39).

The youth advisory board provided input on settings, character design, and social dynamics relevant to vaping. Each session lasted approximately 90 minutes and included: (1) a warm-up ice-breaking activity, (2) improvisational conversation exercises, (3) co-design of dialogue based on prompt lines, and (4) open feedback and discussion. To protect privacy and encourage creative engagement, participants used pseudonyms throughout the entire session. Advisory board members contributed particularly to dialogue development for the social cue scene, which was designed as a backyard barbecue party.

Rapid qualitative methods [30] were used, wherein 2 research team members took notes during the sessions while recording the audio using a Yale-managed instance of Zoom (Zoom Communications, Inc). Immediately after the discussions, the team reviewed audio recordings, revised field notes, and identified key themes. Across sessions, feedback emphasized the importance of situating vaping cues in familiar, everyday social environments and including both solitary and peer-influenced contexts to capture variability in craving and social pressure.

Informed by both expert input grounded in existing literature and UCD, 2 bespoke vaping-related cue scenes (Figure 2) were designed and developed for room-scale VR: a convenience store scene without social pressure and a barbecue party scene with social pressure. Each scene lasts approximately 4 minutes and was optimized for immersion, naturalistic interaction, and ecological validity. The “without social pressure” scene follows prior nicotine cue-reactivity paradigms that contrast socially enriched versus socially neutral contexts to isolate interpersonal influence [31,32]. The convenience store setting reflects a common environment where vaping may occur without peer prompting. While this condition minimizes explicit social influence, contextual differences may still affect responses; therefore, the primary contrast is interpreted as the presence versus absence of peer-driven social pressure rather than a fully context-matched manipulation.

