##### Cue Scene Without Social Pressure

Participants are placed in a virtual convenience store where they are tasked with picking up items from a shopping list (eg, chips, sauces, and drinks) distributed across areas of the store. This task is designed to enhance ecological validity and introduce a mild cognitive distraction, allowing vaping cues to attract participants’ visual attention more naturally. Cue elements include vaping-related posters, vapes behind the counter, and individuals vaping outside the store, visible through the glass window.

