##### Cue Scene With Social Pressure

Participants are immersed in a barbecue party with animated virtual humans, who function both as interaction partners and as background social groups within the scene [33]. Participants are prompted to engage with different clusters of characters and overhear conversations about food, vaping, and school stress. Several characters visibly vape and directly offer an e-cigarette to the participant. This scenario incorporates both visual and verbal peer pressure, reflecting common real-world contexts in which adolescents and young adults may be exposed to vaping.

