After each VR cue scene, participants will remove the headset and complete part 2 of the assessment questionnaire. Part 2 contains self-report measures on craving, presence, social presence, and system usability. An overview of the assessment used in the laboratory visit is listed in Table 2.

**Table 2. T2:** Post–VR cue exposure measures assessing craving, presence, social presence, and system usability.

Measures	Items	Response options
Measured twice, after each VR cue scene		
Craving for vaping or smoking e-cigarettes Visual Analog Scale (VAS) [47]	1 item: “I have a desire for vaping/having an e-cigarette right now.”	A visual scale, ranging from 0 (“Not at all”) to 100 (“Extremely”)
Adapted presence and social presence questionnaire from *Presence (IPQ)* and *Social Presence by Networked Minds Measure of Social Presence* [48,49]	1 item from IPQ measuring general presence: “In the computer-generated world I had a sense of ‘being there’” (general presence item from IPQ). 6 items from the co-presence subscale (*α*=0.84). An example is: “The virtual humans caught my attention.”	5-point Likert scale, ranging from (0) “Do not agree at all” to (4) “Very Likely”
Measured once, after all VR scenes		
System usability by V*irtual Reality System Usability Questionnaire (VRSUQ)* [50]	9 items (*α*=0.679‐0.896). An example is: “The system responded well to my manipulations as expected with no delays.”	5-point Likert scale, ranging from (1) “Strongly disagree” to (5) “Strongly agree”

Eye gaze and physiological data will be recorded continuously during both VR cue scenes as follows:

Eye-gaze behavior: raw eye-tracking data and gaze fixations on predefined regions of interest (eg, vaping-related cues) will be collected and processed into fixation-related metrics such as fixation count, duration, and dwell time.HR and heart rate variability (HRV) will be monitored as indicators of autonomic arousal. HRV will be further processed into standard time-domain metrics, including the root mean square of successive differences, which reflects short-term parasympathetic activity, as well as frequency-domain metrics such as the low-frequency–to–high-frequency ratio, commonly interpreted as an index of sympathovagal balance [51].EDA will also be recorded to measure autonomic arousal and decomposed into tonic skin conductance levels and phasic SCRs using continuous decomposition analysis [52].

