##### Secondary Analyses

For the secondary objective, we will assess associations between multimodal physiological measures and subjective vaping-related outcomes. Correlation and regression analyses will first be conducted to examine pairwise relationships among eye-gaze metrics (eg, total fixations and mean fixation duration), HR, EDA, and subjective measures (eg, craving, dependence scores, and motivation to quit or susceptibility to initiate use). Depending on data distribution, the Pearson or Spearman correlations will be used. Partial correlations or multiple regression models will account for potential covariates such as age, gender, and other substance use.

To further explore multivariate relationships between physiological responses and vaping-related outcomes, exploratory regularized regression analyses will be conducted. Given the pilot sample size, we will use regularized logistic regression with the least absolute shrinkage and selection operator to examine whether aggregated physiological and subjective measures are associated with vaping status (vaper vs nonvaper). Candidate predictors will include summary features derived from eye-gaze behavior (eg, fixation count, proportion of fixation duration on vaping-related cues, and time to first fixation), HRV metrics derived from photoplethysmography signals (including time-domain indices such as root mean square of successive differences and frequency-domain measures such as low-frequency to high-frequency ratio), EDA (eg, mean number of SCRs, mean SCR amplitude, and mean skin conductance level), and relevant subjective responses (eg, craving, presence, and social presence).

Physiological signals will undergo standard preprocessing procedures, including signal quality checks, removal of segments affected by motion artifacts or signal instability, and aggregation into scene-level summary features. Participants will be excluded if more than 15% of their physiological data is missing, and EDA signals will be removed if more than 15% of values are zero or negative, indicating poor sensor contact [56,57]. The regularization parameter will be selected using cross-validation to reduce overfitting [58]. Given the exploratory nature of this analysis and the modest sample size, findings will be interpreted cautiously and used to identify candidate multimodal markers for future confirmatory studies rather than to develop generalizable prediction models.

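### With one scene per level, the cue-condition effect measures social pressure plus context, so a barbecue-versus-store difference should not be reported as an effect of peer pressure alone

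*Protocol article*

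**What the plan says.** The Overview under User-Centered Stimuli Design describes two cue scenes, a convenience store without social pressure and a barbecue party with it. It says the no-pressure scene follows paradigms that "contrast socially enriched versus socially neutral contexts to isolate interpersonal influence". It then concedes that "contextual differences may still affect responses" and concludes: "therefore, the primary contrast is interpreted as the presence versus absence of peer-driven social pressure rather than a fully context-matched manipulation".

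The Primary Aim states a directional hypothesis on this contrast: "We further expect that both groups will show stronger psychological and physiological responses in the social pressure condition than in the no pressure condition". The responses covered are craving, presence, social presence, eye gaze, HR and EDA. Primary Analyses enters cue condition (social pressure versus no social pressure) as the within-subjects factor of a mixed ANOVA.

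The scenes themselves are described as follows.
- **Store:** participants are "tasked with picking up items from a shopping list", a task intended partly as a mild distraction. The only people listed among the cue elements are vaping outside and seen through the window.
- **Barbecue:** animated virtual humans serve as interaction partners and as background groups. Participants engage with clusters of them and "overhear conversations about food, vaping, and school stress". Several characters vape visibly and offer an e-cigarette.

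The example item for the social presence scale in Table 2 reads "The virtual humans caught my attention".

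**The concern.** The concession and the conclusion pull in opposite directions. If context can move the responses, the difference between two unmatched scenes cannot be read as the presence or absence of one ingredient. The word 'therefore' joins a caveat to a reading that the caveat argues against.

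The second part of the primary hypothesis is at stake. A higher barbecue response could be reported as support for a social-pressure effect when it reflects the different task, the interaction with characters, or both. Equally, if the shopping task raised a response in the store, a real pressure effect could be hidden. The pilot is meant to guide later work, so a mislabelled effect would carry forward.

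**Working it through.** **1. What the cue-condition effect estimates.** Write P for the effect of peer pressure on a response and C for the effect of everything else that differs between the scenes. Then

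barbecue mean − store mean = P + C.

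There is one scene per level, so P and C always occur together. No term in the 2×2 ANOVA separates them.

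**2. Whether another design feature separates them.**
- *Counterbalancing* (Study Population and Study Flow) balances order. It leaves C unchanged.
- *The neutral baseline scene* is common to both conditions. Subtracting it gives (barbecue − baseline) − (store − baseline) = barbecue − store, so it drops out.
- *A matched scene*, such as a barbecue without the offer, is not described.
- *Signal summaries:* the physiological processing described under Secondary Analyses includes "aggregation into scene-level summary features". No finer within-scene analysis is described for the primary comparison.

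**3. Whether C can be taken as zero.** Two differences are explicit in the scene descriptions: the task, and the role of the virtual humans (interaction partners in one scene; in the other, the listed people are behind glass). Social presence is the clearest case, because its example item asks about the virtual humans themselves.

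**4. Which primary results are touched.** Let v and n denote vapers and nonvapers.
- *Group main effect:* both groups see the same two scenes, so the comparison averaged over scenes is not affected.
- *Scene main effect:* estimates P + C, averaged over groups.
- *Group × condition interaction:* (Pv + Cv) − (Pn + Cn) = (Pv − Pn) + (Cv − Cn). It is a valid test of group × scene. It can be attributed to pressure only if Cv = Cn, that is, if both groups react equally to the other scene differences.

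**5. The plan's own sample size.** Inputs from Study Design: f=0.25, r=0.50, ε=1.0, two within-subject levels, power 0.80. Alpha is not stated; 0.05 is assumed.

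λ = f² × N × m × ε / (1 − r), with m=2, df 1 and N − 2.

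At N=34, λ = 0.0625 × 34 × 2 / 0.50 = 8.5 and power is 0.807, which reproduces the stated minimum of 34. At N=40, λ = 10 and power is 0.869. Under the same inputs the scene main effect has the same power.

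**6. Illustration of a pure context shift.** Set P=0. With equal scene variances, the SD of the within-person difference is SD × √(2(1 − r)) = SD × √(2 × 0.50) = SD. A shift of d single-scene SDs is therefore a standardised paired effect of d. The noncentrality is d√N on N − 2 df, two-sided 0.05. The values of d are assumptions.

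| Context shift (SD) | Noncentrality, N=40 | Chance of a significant scene effect, N=40 | Same, N=34 |
|---|---|---|---|
| 0 | 0 | 0.05 | 0.05 |
| 0.1 | 0.632 | 0.09 | 0.09 |
| 0.2 | 1.265 | 0.23 | 0.20 |
| 0.3 | 1.897 | 0.46 | 0.40 |
| 0.4 | 2.530 | 0.69 | 0.62 |
| 0.5 | 3.162 | 0.87 | 0.81 |

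The chance rises with N, so this is a problem of identification and not of sample size. A shift of the opposite sign and equal size would cancel a true pressure effect.

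**The case against.** The strongest reply is that the authors have already said this. The Overview states that context may matter and that the scenes are not fully matched. Its sentence can be read as a plain description: the conditions differ by the presence of peer pressure and are not otherwise equated. Using both a solitary and a peer setting was deliberate and came from focus-group feedback, and interviews about each scene will help interpret the results. The study is also powered for the interaction, and a context shift common to both groups cancels from it.

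Much of this stands. The problem is partly disclosed, and the central user-versus-nonuser comparison is sound. But the disclosure ends by keeping the pressure interpretation, the hypothesis and the ANOVA factor carry no caveat, and the Limitations are silent on it. The interviews can add context but cannot separate P from C in the quantitative test.

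A reader might infer more than the documents support:
- *That the scenes differ in movement or in the number of virtual humans.* Both scenes are room-scale, no movement data or character counts are given, and the store description lists cue elements, not every character. These differences are plausible but inferred.
- *That all six co-presence items favour the barbecue.* Only one item is shown.
- *That participants converse at the barbecue.* The text says they engage and overhear.
- *That scene-level aggregation throws away the data needed.* Recording is continuous, and the aggregation text appears under Secondary Analyses.
- *That 46% to 87% are false-positive rates of the test.* The scene difference would be real; the error would lie in its label. The shifts are assumed.

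**Conclusion.** The point holds as one of interpretation. As designed, the cue-condition main effect is a barbecue-versus-store effect, and it cannot by itself support the social-pressure part of the primary hypothesis. This follows from the one-scene-per-level design and needs no numerical assumption beyond C possibly differing from zero, which the article itself grants.

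The size cannot be determined from the documents. Under the plan's r=0.50, N=40 and an assumed two-sided 0.05, context shifts of 0.3 to 0.5 SD would produce a significant effect labelled as pressure 46% to 87% of the time with no pressure effect present.

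A reader might conclude that the whole primary analysis is compromised. It is not: the group main effect stands, the interaction stands as group × scene, and the stated sample size is reproduced and need not change.

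**What to change.** 1. In the Primary Aim, the stimuli Overview and Primary Analyses, define the within-subject factor as scene (barbecue with social pressure versus store without). State that a scene effect will not be reported as an effect of peer pressure alone, and that attributing the interaction to pressure assumes equal reactions of both groups to the other scene differences.
2. Report the scene effect on social presence as a manipulation check, not as a test of the hypothesis.
3. Add the confounding of scene and pressure to the Limitations.
4. Optionally, and only as exploratory, compare windows around the e-cigarette offers with windows of non-vaping conversation within the barbecue, by group. This requires time-stamped scene events, which the article does not describe. It would not isolate pressure either, because the windows also differ in vaping content, direct address and timing, and short windows give noisier HR and EDA estimates.

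Items 1 to 3 are wording changes and need no new data or participants. With data from 7 participants collected as of March 2026, they can still be made early in data collection. The downside is that the between-scene result carries a weaker claim.
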